### Participants

Recruitment will be conducted through outpatient and inpatient departments of geriatrics, spine, and trauma at Xi’an Hospital of TCM.

### Inclusion criteria

Participants are eligible if they meet ALL of the following: Voluntary agreement to take part and signed informed consent.

Diagnosis of primary osteoporosis according to Western-medicine criteria. TCM syndrome differentiation of “blood-stasis syndrome”. ndividuals aged between 45 and 70 years, regardless of gender.Low-back or limb-joint pain for ≥3 months.

### Exclusion criteria

Participants will be excluded if ANY of the following apply:

Fracture within the past 6 months.

Concomitant endocrine or metabolic diseases (hyperparathyroidism, Cushing’s syndrome, hyperthyroidism, gonadal hyper-function, diabetes), hematological diseases (myeloma, leukaemia), severe gastrointestinal diseases, or psychiatric/neurological disorders. Low-back pain attributable to lumbar-disc herniation, cervical spondylosis, or other clear causes.

Severe cardio-cerebrovascular disease, hepatic or renal insufficiency. Psychosis or inability to give informed consent. Participation in another clinical trial or completion of another drug trial within 3 months.

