Visit window		−3∼0	Day 30 of treatment	Day 60 of treatment	Day 90 of treatment
Basic history taking					
Informed-consent signature		×	​	​	​
Demographics		×	​	​	​
General data form		×	​	​	​
Medical and prior-treatment history		×	​	​	​
Inclusion/exclusion check		×	​	​	​
Randomisation and enrolment		×	​	​	​
Screening variables					
Bone-mineral density (BMD)		×	​	​	​
Treatment administration					
Test group		​	×	×	×
Control group		​	×	×	×
Efficacy end-points (assessment visits)					
BMD measurement		×	​	​	×
TCM syndrome score		×	×	×	×
Pain score (VAS)		×	×	×	×
Bone-turnover markers (β-CTX, PINP)		×	×	×	×
Inflammatory cytokines (TNF-α, IL-1)		×	×	×	×
Blood-stasis syndrome score		×	×	×	×
Blood-cell indices		×	×	×	×
Safety observations					
Height		×	​	​	×
Blood pressure		×	​	​	×
Electrocardiogram		×	​	​	×
Haematology		×	​	​	×
Liver function		×	×	×	×
Renal function		×	×	×	×
Coagulation profile		×	​	​	×
Adverse-event log		​	×	×	×
Other items					
Concomitant medication / therapy		×			
Study closeout	Withdrawals and drop-outs	×			
	Compliance and safety evaluation form	×			
	Abnormalfindings record	×			
	Studycompletion status	×			
Review & sign-off		×			

Rumo zhentong Yin—composed of Ruxiang (frankincense), Moyao (myrrh), Xuejie (dragon’s blood), Jiangxiang (dalbergia wood), Sumu (sappan wood), Gansong (nardostachys), Xixin (asarum), and Tubiechong (ground beetle)—is an empirical formula created by national TCM master [name] for blood-stasis pain. Although preclinical studies support the anti-inflammatory, analgesic, and bone-protective effects of its ingredients, robust clinical evidence is still lacking (Shima et al., 2016; Lisowska et al., 2018).

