### Withdrawal/discontinuation criteria

Participants will be withdrawn or discontinued if ANY of the following occur: violation of inclusion criteria or fulfillment of any exclusion criterion during the study. Receipt of study treatment for fewer than 30 consecutive days or evidence of poor compliance. Occurrence of serious side-effects, adverse reactions, or allergic reactions. Initiation or modification of concomitant therapies that could influence outcomes without prior approval from the investigator. Withdrawal of informed consent by the participant or their legally authorized representative. Significant disease progression or the development of a new medical condition requiring urgent or alternative.

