### Intervention

Basic therapy: Alendronate sodium (MSD PHARMA [SINGAPORE] PTE.LTD.; Import Drug Registration No. H20160100; 70 mg) 70 mg orally once weekly; Calcium carbonate D_3_ (Wyeth Pharmaceutical Co., Ltd.; National Drug Approval No. H10950029; 600 mg) 600 mg orally daily; Calcitriol soft capsules (Catalent Germany Eberbach GmbH; Import Drug Registration Nos. H20140597 & H20140598; 0.25 µg) 0.5 µg orally once daily; and Elcatonin injection (Shandong Luye Pharmaceutical Co., Ltd.; National Drug Approval No. H20040338; 1 mL:10IU)was administered intramuscularly at 1 mL per dose,twice weekly (all injections were administered by trained hospital nurses). Treatment duration: 3 months. Control group: Conventional intervention only.

Observation group: Conventional intervention plus Rǔ-Mò Analgesic Decoction (10 g Frankincense, 10 g Myrrh, 3 g Dragon’s Blood, 6 g Dalbergia wood, 10 g Sappan wood, 10 g Chinese spikenard, 3 g Asarum root, 6 g Ground beetle).Table 2 summarises the key components of Rumo zhentong Yin.

**TABLE 2 T2:** Key Components of Rumo zhentong Yin.

Chinese name	Latin name/English name	Source organism/Plant part	Quantity (g per day)	Components of Rumo zhentong Yin
Ruxiɑng	Olibanum	Boswellia sacra Flück	10	[figure not shown]
Moyɑo	Myrrha	Commiphora wightii	10	[figure not shown]
Xuejie	Draconis sanguis	Daemonorops draco Bl	3	[figure not shown]
Jiɑngxiɑng	Dalbergiae odoriferae lignum	Dalbergia odorifera T.C.Chen	6	[figure not shown]
Sumu	Sappan lignum	Biancaea sappan	10	[figure not shown]
Gɑnsong	Nardostachyos radix et rhizoma	Nardostachys jatamansi (D.Don) DC.	10	[figure not shown]
Xixin	Asari radix et rhizoma	Asarum sieboldii miq.	3	[figure not shown]
Tubiechong	Eupolyphaga seu polyphaga	Eupolyphaga sinensis	6	[figure not shown]
​	​	土鳖虫不是植物,所以这是他的学名不是 source plant	​	​

All herbal ingredients of Rumo Zhentong Yin were provided by the Pharmacy Department of Xi’an Hospital of Traditional Chinese Medicine and met the quality standards of the Chinese Pharmacopoeia (2020 Edition). Each batch underwent hospital incoming quality inspection. Processing was conducted in accordance with hospital standards; impurities and non-medicinal parts were removed. Specifically, only dried roots and rhizomes of Asarum were used, excluding aerial parts.

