#### Concomitant-therapy rules

Throughout the trial, participants are prohibited from using any concomitant medication or intervention that could interfere with the assessment of efficacy or safety. If a participant has a chronic comorbidity requiring ongoing treatment, all concurrent therapies must be documented in the Case Report Form (CRF).

Throughout the trial, participants are forbidden to use any concomitant medication or intervention that could interfere with the assessment of efficacy or safety. If a participant suffers from a chronic co-morbidity that requires continuous treatment, all concurrent therapies must be documented in the Case Report Form (CRF).

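### Eligibility leaves routine-care drug use before baseline open and the stated analysis does not adjust for it, so precision may be lost and VAS conditions may differ between baseline and follow-up

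*Protocol article*

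**What the plan says.** All references are to the protocol article.

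- **Inclusion criteria.** Participants must meet every item on the list. The pain item is "Low-back or limb-joint pain for ≥3 months", with no condition on past or current treatment.
- **Exclusion criteria.** Any one item excludes. Two items carry a time window: "Fracture within the past 6 months", which is not a treatment, and "Participation in another clinical trial or completion of another drug trial within 3 months", which covers drugs only when taken in a trial.
- **Table 1.** Screening runs from day −3 to day 0 and includes baseline VAS, β-CTX and PINP. "Medical and prior-treatment history" is recorded there, and as extracted the concomitant-medication mark also stands in the screening column. Neither record has a stated use in eligibility, allocation or analysis.
- **Intervention.** Both arms receive alendronate, calcium carbonate D3, calcitriol and elcatonin. The comparator is defined by "Control group: Conventional intervention only".
- **Concomitant-therapy rules.** "Throughout the trial, participants are prohibited from using any concomitant medication or intervention that could interfere with the assessment of efficacy or safety".
- **Withdrawal/discontinuation criteria.** One trigger is "Initiation or modification of concomitant therapies that could influence outcomes without prior approval from the investigator".
- **Randomisation and blinding.** Allocation is simple, with no stratification. Statisticians stay masked until after database lock.
- **Statistical analysis.** Continuous endpoints are compared between arms by t-test or Mann–Whitney U, with no covariate named.

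**The concern.** Participants have diagnosed osteoporosis and at least three months of pain, and they come from geriatrics, spine and trauma departments. The Introduction and Discussion name anti-osteoporotic drugs and NSAIDs as current management. The criteria admit a patient who has taken such drugs in ordinary care up to the day of randomisation.

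Two things follow for those patients.

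1. Someone already on the background drugs may have had part of their effect on pain and bone markers before baseline, and so may change less afterwards than someone starting them.
2. Someone on an analgesic at day 0 falls between two rules. If the drug counts as interfering, continuing it is barred. Stopping it is a modification that triggers withdrawal unless the investigator approves. If it is stopped, baseline VAS is scored with the analgesic and later VAS without it.

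At stake are the precision of a comparison planned on a VAS difference of only 0.38, and the meaning of within-group change from baseline.

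**Working it through.** **Inputs from the Sample size section.** VAS improvement 2.45 ± 0.53 against 2.07 ± 0.53, so the difference is 2.45 − 2.07 = 0.38. Two-sided α = 0.05, power 0.95, 51 per arm, 57 per arm after 10% attrition.

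**The plan's own figure.** n = 2 × (0.53/0.38)² × (1.960 + 1.645)² = 50.6, so 51 per arm. 51/0.90 = 56.7, so 57 per arm and 114 in total. The noncentral-t calculation needs 51.5 and gives power 0.948 at 51. The stated size reproduces.

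**Inputs not in the document (assumptions).**
- p, the share of prior users: 20% to 40%.
- g, the shortfall in VAS improvement of prior users against new starters: 0.3, 0.5 or 1.0 points.
- 0.53 is the SD within each type of patient, that is, it does not already include the mix.
- The treatment effect is 0.38 in both types.

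**Spread from the mix.** SD = √(0.53² + p(1 − p)g²), with 0.53² = 0.2809. Power is for the two-sample t-test at 51 per arm and difference 0.38.

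| g | p | p(1 − p)g² | SD | Power |
|---|---|---|---|---|
| none | – | 0 | 0.53 | 0.95 |
| 0.3 | 0.2 | 0.0144 | 0.54 | 0.94 |
| 0.3 | 0.4 | 0.0216 | 0.55 | 0.93 |
| 0.5 | 0.2 | 0.0400 | 0.57 | 0.92 |
| 0.5 | 0.4 | 0.0600 | 0.58 | 0.90 |
| 1.0 | 0.2 | 0.1600 | 0.66 | 0.82 |
| 1.0 | 0.4 | 0.2400 | 0.72 | 0.75 |

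**Chance imbalance.** With 57 per arm, the difference between arms in the share of prior users has standard deviation √(2p(1 − p)/57), which is 0.075 at p = 0.2 and 0.092 at p = 0.4. An imbalance of 10 percentage points or more in either direction has exact binomial probability of about 0.20 and 0.29. Such an imbalance shifts the contrast by 0.10 × g:
- g = 0.3: 0.03 points, 8% of 0.38.
- g = 0.5: 0.05 points, 13% of 0.38.
- g = 1.0: 0.10 points, 26% of 0.38.

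This shift is the same variation that the p(1 − p)g² term already puts into the SD. It is another view of one effect and must not be added to the power loss.

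**What adjustment does.** If yes/no coding captures prior use fully, the p(1 − p)g² term leaves the residual variance. Under these assumptions the SD then returns to 0.53 and power to about 0.95, apart from a few degrees of freedom.

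**The case against.** Both arms receive the same background therapy and allocation is random, so prior use cannot systematically favour either arm. Admitting pre-treated patients to an add-on trial is a legitimate pragmatic choice. This stands, and it limits the point to precision and interpretability.

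A reader might infer more in four places, and the document does not support it.

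- **That chance imbalance biases the result.** Imbalance under randomisation is random error, already allowed for in the test's error rate.
- **That the power loss is large.** Only the 1.0-point gap gives a large loss, and it has no source. At 0.3 points the loss is one or two percentage points.
- **That established users cannot show the planned 2.07-point fall.** The Sample size section attributes that figure to Western medicine alone. It does not say that the pilot patients were newly starting it. If the pilot also enrolled a mix, 0.53 already contains this spread and no inflation follows.
- **That pre-treated patients will be common, or that every baseline is a treated value.** The document gives no rate of use, and the remarks on usual management are general.

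The analgesic problem also depends on reading. The ban names no drug class, and since Table 1 counts screening as a study phase, the ban might be meant to cover baseline. That ambiguity supports reconciling the text; it does not settle it. Lastly, covariates are often left to an analysis plan, and none is shown. But the article does name its between-group tests, and neither takes a covariate.

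**Conclusion.** The gap is real. The eligibility lists are introduced as complete, the one treatment look-back covers trials only, and neither the in-trial ban nor the withdrawal rule clearly reaches back before baseline. Prior-treatment data are collected without a stated use, allocation is unstratified, and the stated comparison is unadjusted.

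The likely harm is modest: power at 51 per arm somewhere between 0.94 and 0.75 instead of 0.95, with most of that range set by an unsourced gap. It rests on the assumed share of prior users, the assumed gap, and a planning SD free of the mix. If the last assumption fails, the planned power stands, but adjustment could still gain precision. The possible mismatch of analgesic conditions needs no assumption about size, because it follows from rules that do not fit together. Systematic bias between arms is not shown.

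**What to change.** 1. **Analysis.** Before unblinding, replace the t-test or Mann–Whitney comparison of VAS, β-CTX and PINP with a prespecified ANCOVA, or a mixed model over the visits. Include treatment, the baseline value, prior bone-active drug use (yes/no) and baseline analgesic use (yes/no). Code both items blind to arm from the screening history and the concomitant-medication record in Table 1. This also covers patients randomised since enrolment began on 12 September 2025. If an existing analysis plan already does this, the article's Statistical analysis section should say so.
2. **Text.** Reconcile the Concomitant-therapy rules and the Withdrawal/discontinuation criteria with the day −3 to 0 baseline, so that VAS is scored under consistent analgesic conditions at every visit. Which analgesic rule applies, and whether any look-back or wash-out is adopted, is for the sponsor's clinicians; the documents support no particular length.

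**Cost.** The primary analysis model changes and must be documented as an amendment made while masked. Two items must be coded, and the model uses a few degrees of freedom. No new data are needed if the screening records are complete enough to code.

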### Withdrawal/discontinuation criteria

Participants will be withdrawn or discontinued if ANY of the following occur: violation of inclusion criteria or fulfillment of any exclusion criterion during the study. Receipt of study treatment for fewer than 30 consecutive days or evidence of poor compliance. Occurrence of serious side-effects, adverse reactions, or allergic reactions. Initiation or modification of concomitant therapies that could influence outcomes without prior approval from the investigator. Withdrawal of informed consent by the participant or their legally authorized representative. Significant disease progression or the development of a new medical condition requiring urgent or alternative.

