### Outcomes

Primary endpoints: Pain score: Visual Analogue Scale (VAS); Mechanism indicators: 1.Bone-mineral density (BMD); 2.Bone-turnover markers: β-CTX and PINP; 3.Inflammatory cytokines: TNF-α and IL-1.

Secondary endpoints:1.Blood-stasis syndrome score; 2.Hematological indices: serum MCV, RDW-CV, MPV and PDW.

Safety endpoints:Height, blood pressure, 12-lead ECG, routine hematology, liver and renal function tests, and coagulation profile.

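### The withdrawal rule turns some entry criteria into a continuing test, so withdrawal can depend on outcomes the trial measures (liver and renal function, possibly blood-stasis syndrome)

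*Protocol article*

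**What the plan says.** Under Withdrawal/discontinuation criteria, the protocol article states "Participants will be withdrawn or discontinued if ANY of the following occur". The first item is "violation of inclusion criteria or fulfillment of any exclusion criterion during the study". Separate items in the same list cover adverse reactions and new medical conditions.

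The criteria to which the clause refers include:

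- Inclusion: "Diagnosis of primary osteoporosis according to Western-medicine criteria", a TCM diagnosis of blood-stasis syndrome, and "Low-back or limb-joint pain for ≥3 months".
- Exclusion: "Fracture within the past 6 months" and "Severe cardio-cerebrovascular disease, hepatic or renal insufficiency".

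Under Outcomes, VAS pain and BMD are listed with the primary endpoints, and the blood-stasis score is a secondary endpoint. The safety endpoints include "12-lead ECG, routine hematology, liver and renal function tests, and coagulation profile". Table 1 places VAS, the blood-stasis score, liver function and renal function at screening and at days 30, 60 and 90. It places BMD at screening and day 90, and the inclusion/exclusion check at screening only.

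Study design and setting says that the intervention runs for up to 3 months and gives three exceptions: withdrawn consent, loss to follow-up and death. Statistical analysis says that missing values are filled by LOCF.

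**The concern.** Entry criteria describe who may be randomised. Once they are applied again during treatment, any criterion that treatment can change becomes a post-randomisation filter. If that criterion is also something the trial measures, the filter selects on the outcome.

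This could act in two directions. A participant who develops hepatic or renal insufficiency meets a withdrawal trigger because of a safety result. If withdrawal ends follow-up, the later course of that harm is not recorded. On a literal reading, a participant whose blood-stasis syndrome resolves stops meeting an inclusion criterion and could be withdrawn for having responded. If the herbal arm is better, it loses more such participants, and the contrast shrinks. The 10% attrition allowance in the sample size covers lost numbers, not this kind of bias.

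**Working it through.** **1. Which criteria overlap with outcomes**

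| Entry criterion | Matching outcome | Can the clause act before day 90? |
|---|---|---|
| Hepatic or renal insufficiency (exclusion) | Liver and renal safety tests, days 30, 60, 90 | Yes. The words on arising during the study plainly govern the exclusion half of the clause |
| Blood-stasis syndrome (inclusion) | Blood-stasis score, days 30, 60, 90 | Yes on a literal reading. No score at which the diagnosis lapses is given |
| Pain for at least 3 months (inclusion) | VAS | Weak. It is a duration, with no VAS threshold |
| Primary osteoporosis (inclusion) | BMD | Not through a scheduled test. BMD is repeated only at day 90 |
| Recent fracture (exclusion) | None listed | A new fracture meets the clause, but fracture is not a listed endpoint |
| Consent, age, endocrine or haematological disease, other trials | None of the efficacy endpoints | Not an efficacy-outcome route |

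One firm harm route and one plausible responder route remain.

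**2. What is lost on the harm route.** If insufficiency is found at day 30 and withdrawal ends follow-up, the liver and renal tests at days 60 and 90 are lost, two of the three on-treatment assessments. Whether withdrawal ends follow-up is not stated.

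**3. Internal conflict.** The design section gives three reasons for the intervention to end, and eligibility is not among them. The withdrawal section adds eligibility and other triggers. Table 1 schedules no eligibility re-check after screening.

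**4. The plan's own sample size, for reference.** Inputs from Sample size: improvements 2.45 and 2.07, SD 0.53, two-sided α 0.05, power 0.95.

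n per arm = 2 × [(1.960 + 1.645) × 0.53 / 0.38]² = 50.6, rounded up to 51. Then 51 / 0.90 = 56.7, rounded up to 57 per arm, 114 in total. Both figures reproduce.

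**5. Illustration of the responder route.** The document gives no rate of on-study criterion failure, so the trigger must be assumed. Take improvements as normal with the planning values, and suppose that those above a cut-off c are withdrawn. For an arm with mean μ and SD σ, let a = (c − μ)/σ.

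- If they are dropped: mean = μ − σφ(a)/Φ(a).
- If they are held at c: mean = μΦ(a) − σφ(a) + c[1 − Φ(a)].

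For c = 3.0:

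- Treatment: a = 0.55/0.53 = 1.038, Φ = 0.850, φ = 0.233. Removed 15.0%. Mean 2.305 if dropped, 2.409 if held.
- Control: a = 0.93/0.53 = 1.755, Φ = 0.960, φ = 0.086. Removed 4.0%. Mean 2.023 if dropped, 2.061 if held.

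| Assumed cut-off | Difference if dropped | Difference if held at cut-off |
|---|---|---|
| 2.75 | 0.23 (−39%) | 0.31 (−18%) |
| 3.0 | 0.28 (−26%) | 0.35 (−9%) |
| 3.25 | 0.33 (−14%) | 0.37 (−3%) |

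**6. Dependence on LOCF.** A simulation (57 per arm, 20,000 runs) withdrew the best 10% of improvers overall. With these dropped, the difference was 0.28 and power 87%, against 95% for the same loss at random. With their values frozen at two thirds of final improvement the difference was 0.25, and at 90% it was 0.34. Carrying forward can thus do better or worse than dropping, depending on how early the last value was taken.

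**The case against.** The strongest reply is that this is loose wording and not a design that removes responders. Table 1 checks eligibility only at screening, the inclusion list is framed as a test for entry, and a violated inclusion criterion can simply mean a participant found after entry to have been ineligible. That reading is reasonable, and it is why the responder route is put forward only as a literal reading. It does not reach the exclusion half, which expressly covers criteria met during the study.

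A reader might go further and infer that the entry criteria as a whole are the trial's outcomes, that patients whose pain resolves will be removed, or that the planned effect will shrink by about a quarter. The document supports none of these. Most criteria are not outcomes, the pain criterion has no VAS threshold, and the 26% figure needs both an invented VAS trigger and the dropping of withdrawn patients. Nothing in the article excludes them from analysis, and the LOCF rule suggests that their earlier values stay in.

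A reader might also infer that harms are hidden. A harm that triggers withdrawal has been observed. Table 1 has an adverse-event log and closeout forms, and a data monitoring committee reviews safety. The separate adverse-reaction trigger would lead to many of the same discontinuations anyway. What stands is narrower: the later course of the harm may go unrecorded, because no trigger is said to preserve follow-up.

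Finally, a condensed article may leave follow-up after discontinuation and the analysis sets to fuller documents. That is accepted. The point rests on the rule the article does state, and on its conflict with the design section and Table 1.

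**Conclusion.** The point holds in a limited form. The clause makes some entry criteria a continuing test, at odds with Table 1 and with the three reasons given in the design section. For new hepatic or renal insufficiency, withdrawal depends on a safety outcome as the rule is written. For resolved blood-stasis syndrome it does so only on a literal reading. The consequences are possible truncation of harm follow-up and, where responders are withdrawn, a bias towards no effect in the cases examined. None of those cases produces a false claim of benefit.

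The size is unknown. At assumed cut-offs from 2.75 to 3.25 the planned 0.38 becomes 0.23 to 0.33 if withdrawn patients are dropped, and 0.31 to 0.37 if they are held at the cut-off. These figures assume normality, the planning means and SD, and a VAS trigger that no entry criterion contains. They show direction and sensitivity and are not a forecast. The harm side was not quantified.

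**What to change.** Reconcile Table 1, Study design and setting, the inclusion, exclusion and withdrawal sections, and the LOCF statement, so that they say the following:

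- Eligibility criteria apply at entry. Ineligibility found later is recorded as a protocol deviation.
- Improvement in a qualifying condition, including resolution of blood-stasis syndrome, is not a reason for withdrawal.
- Stopping study treatment is distinct from leaving follow-up. Participants who stop treatment still attend the remaining Table 1 assessments and stay in the analysis.

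When study treatment should stop after a new medical event is a clinical rule. The passages conflict on it, and the investigators must reconcile them. No rule is proposed here.

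The cost is one short amendment while recruitment is open (registered to close on 31 December 2026), through the ethics route the article already describes. No new visits or tests are needed. The small downside is that some off-treatment values enter the analysis.

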### Drop-out criteria

Participants are considered drop-outs if ANY of the following occur: Failure to attend scheduled visits on time.

Are lost to follow-up.

Voluntarily withdraw before completing the full course.

Do not adhere to the protocol to an extent that efficacy evaluation is compromised.

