### Randomisation and blinding

Simple randomisation was used. The allocation sequence was generated using SPSS version 24.0. Each unique allocation code was placed in a sequentially numbered, opaque, sealed envelope (numbered 1–114) and stored by an independent custodian. After obtaining informed consent, the next envelope in sequence was opened, and the participant was assigned to either the control or treatment group (n = 57 per group). Because the two interventions could not be blinded to participants, only the outcome assessors, data managers, and statisticians were masked to group assignment. In the Case Report Form (CRF), group labels were replaced with the identifiers“A” and “B.” The master randomisation list (containing the sealed code linking A/B to actual groups) was generated by an external statistician using SAS software and is securely stored by the study administrator. It will remain concealed until after final database lock.

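### Withdrawal and drop-out rules for post-randomisation adherence events do not separate stopping treatment from leaving follow-up, which puts the randomised comparison at risk

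*Protocol article*

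**What the plan says.** The Withdrawal/discontinuation criteria open in mandatory terms: "Participants will be withdrawn or discontinued if ANY of the following occur: violation of inclusion criteria or fulfillment of any exclusion criterion during the study". The list that follows includes:

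- "Receipt of study treatment for fewer than 30 consecutive days or evidence of poor compliance"
- "Initiation or modification of concomitant therapies that could influence outcomes without prior approval from the investigator"

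The Drop-out criteria class a participant as a drop-out for any one of several events, including:

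- "Failure to attend scheduled visits on time"
- "Do not adhere to the protocol to an extent that efficacy evaluation is compromised"

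Neither section says whether these patients keep attending visits or stay in the analysis. The Statistical analysis section names LOCF for missing values. Table 1 schedules the VAS at screening and on days 30, 60 and 90.

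On masking, the article states: "Because the two interventions could not be blinded to participants, only the outcome assessors, data managers, and statisticians were masked to group assignment". Both arms receive standard care, and the treatment arm adds the decoction, with no placebo.

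On other therapies, the Concomitant-therapy rules say that "participants are prohibited from using any concomitant medication or intervention that could interfere with the assessment of efficacy or safety". The withdrawal rule applies only where the investigator has not approved the therapy beforehand.

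**The concern.** Apart from an eligibility error already present at entry, these events happen after randomisation and may be consequences of treatment. Poor compliance with the decoction, or a reaction to it, can occur in one arm only, and patients know which arm they are in. Two triggers (poor compliance, and non-adherence that undermines the efficacy assessment) carry no threshold.

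Several triggers cannot work as rules for stopping treatment. A patient with fewer than 30 consecutive days of treatment has already stopped or interrupted it, so the rule can only change that patient's status in the trial. The same is true of a late visit and of the efficacy-evaluation trigger. Read as written, they end participation, and the remaining VAS scores are then never collected.

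What is at stake is whether the day-90 contrast estimates the effect of adding the decoction in everyone randomised, or a contrast shaped by who stayed.

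**Working it through.** **Inputs from the Sample size section.** Mean VAS improvement 2.45 (combination) and 2.07 (Western medicine alone), SD 0.53 in each arm; two-sided α 0.05, power 0.95, 1:1 allocation; 51 per arm, raised to 57 per arm (114) for 10% attrition.

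**The plan's own figure.** n per arm = 2(1.960 + 1.645)² × 0.53² / 0.38² = 50.6, so 51. Then 51/0.9 = 56.7, so 57 per arm and 114 in total. The stated size reproduces (the noncentral-t version gives 52 before attrition). Sample size is not the problem here.

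**Illustration 1: planned effect among those who stay.** Assumptions not in the documents: 10% of the decoction arm is affected, the other 90% improve by 2.45, and the control arm is complete at 2.07.

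- Affected patients excluded: 2.45 − 2.07 = 0.38.
- Affected patients improve like controls: arm mean 0.9 × 2.45 + 0.1 × 2.07 = 2.412, so the all-randomised difference is 2.412 − 2.07 = 0.342. Exclusion overstates it by 0.38/0.342 = 1.11.
- Affected patients do not improve at all: arm mean 0.9 × 2.45 + 0.1 × 0 = 2.205, so the difference is 2.205 − 2.07 = 0.135. Exclusion overstates it by 0.38/0.135 = 2.8.
- LOCF for patients who leave before day 30: baseline is the only value to carry forward, so improvement is scored as zero and the difference is again 0.135, whatever those patients really experienced. If they in fact improved like controls, LOCF reports 0.135 where the all-randomised value is 0.342.
- Both arms lose 10% before day 30 and LOCF scores all of them zero: 0.9 × (2.45 − 2.07) = 0.342.

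So the error can run in either direction, depending on how the lost patients are handled.

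**Illustration 2: no true effect.** Assumptions: a fraction f of the decoction arm only is left out of the analysis, and those patients improve g SDs less than their arm's mean. The false difference is f × g × 0.53 / (1 − f). The type I error is from a two-sided t-test with 57 controls and the decoction patients who remain.

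| f | Remaining in decoction arm | False difference, g = 0.5 to 1.0 | Type I error |
|---|---|---|---|
| 5% | 54 | 0.014 to 0.028 | 5.2% to 5.9% |
| 10% | 51 | 0.029 to 0.059 | 5.9% to 8.8% |
| 20% | 46 | 0.066 to 0.133 | 9.6% to 23.9% |

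The 20% row is 17% to 35% of the planned 0.38.

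**Cost in sample size of analysing everyone.** t-test power at the planned effect is 96.7% with 57 per arm and 94.8% with 51. No larger trial is needed under the plan's figures, provided non-adherence does not dilute the effect.

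**The case against.** A reader might infer that these patients are deleted from the analysis and that the randomised comparison is therefore broken. The article does not say so. It speaks of withdrawal, discontinuation and drop-out, and its use of LOCF suggests that incomplete patients may be kept. Analysis sets are commonly left to a full protocol or analysis plan that is not shown, so their absence here is no finding.

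A reader might also take the 2.8-fold inflation as the size of the problem. It needs both deletion and zero improvement. Zero is 2.45/0.53 = 4.6 SDs below the arm mean, and every patient is assigned alendronate, calcium with vitamin D3, calcitriol and elcatonin. If those who stop the decoction improve like controls, the factor is 1.11.

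Other stronger readings also fail:

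- The trial is not simply unblinded: outcome assessors, data managers and statisticians are masked.
- The article does not say who applies the criteria, so it cannot be asserted that unmasked staff do.
- Control pain is not untreated, and controls can also meet the compliance and adverse-reaction triggers.
- Added therapy triggers withdrawal only without prior approval. If it removed controls with more pain, the contrast would shrink, so the net direction is not known.
- The missing tolerance around a visit date is detail that an article may leave out. No weight is placed on it.

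All of this stands and limits the claim. It does not remove the core. If visits stop at withdrawal, the day-60 and day-90 VAS scores do not exist, and no analysis plan can restore them. LOCF does not repair that for a patient who has only a baseline score.

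**Conclusion.** The point holds as a risk that the wording creates, not as a stated exclusion from analysis. The rules are mandatory, rest on adherence events after randomisation, can act unequally between arms, and do not say that follow-up continues.

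The size rests on assumptions the documents cannot settle. With 10% of the decoction arm affected, the all-randomised difference could lie anywhere from 0.135 to 0.342 while the patients who stayed show 0.38. With no true effect, one-sided exclusion of 10% gives a modest distortion (type I error 5.9% to 8.8%), and 20% a material one (9.6% to 23.9%). Similar losses in both arms would do less harm.

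Separately, the outright prohibition in the Concomitant-therapy rules and the approval route implied in the withdrawal criteria must be reconciled.

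**What to change.** - State that stopping treatment, poor compliance, a late visit or added therapy does not end follow-up.
- Collect the VAS on days 30, 60 and 90 from every randomised patient unless consent for data collection is withdrawn.
- Analyse all randomised patients in their assigned arm.
- Use the withdrawal and drop-out criteria only to define a secondary per-protocol set.
- Reconcile the two sections on concomitant therapy. Which rule should apply is for the sponsor and investigators to decide.

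The clinical reasons for stopping treatment stay as they are. The cost is a wording amendment, slightly more follow-up work at visits already scheduled, and a possibly smaller estimated effect. The Trial status section keeps recruitment open until 31 December 2026, so an early change protects the most data; scores not collected cannot be recovered later.
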